# Randomised double-blind phase 3 clinical study testing impact of atorvastatin on prostate cancer progression after initiation of androgen deprivation therapy: study protocol

**DOI:** 10.1136/bmjopen-2021-050264

**Published:** 2022-04-29

**Keywords:** prostate disease, clinical trials, urological tumours

## Abstract

**Introduction:**

Blood cholesterol is likely a risk factor for prostate cancer prognosis and use of statins is associated with lowered risk of prostate cancer recurrence and progression. Furthermore, use of statins has been associated with prolonged time before development of castration resistance (CR) during androgen deprivation therapy (ADT) for prostate cancer. However, the efficacy of statins on delaying castration-resistance has not been tested in a randomised placebo-controlled setting.

This study aims to test statins’ efficacy compared to placebo in delaying development of CR during ADT treatment for primary metastatic or recurrent prostate cancer. Secondary aim is to explore effect of statin intervention on prostate cancer mortality and lipid metabolism during ADT.

**Methods and analysis:**

In this randomised placebo-controlled trial, a total of 400 men with de novo metastatic prostate cancer or recurrent disease after primary treatment and starting ADT will be recruited and randomised 1:1 to use daily 80 mg of atorvastatin or placebo. All researchers, study nurses and patients will be blinded throughout the trial. Patients are followed until disease recurrence or death. Primary outcome is time to formation of CR after initiation of ADT. Serum lipid levels (total cholesterol, high-density lipoprotein (HDL), low-density lipoprotein (LDL) and trigyserides) are analysed to test whether changes in serum cholesterol parameters during ADT predict length of treatment response. Furthermore, the trial will compare quality of life, cardiovascular morbidity, changes in blood glucose and circulating cell-free DNA, and urine lipidome during trial.

**Ethics and dissemination:**

This study is approved by the Regional ethics committees of the Pirkanmaa Hospital District, Science centre, Tampere, Finland (R18065M) and Tarto University Hospital, Tarto, Estonia (319/T-6). All participants read and sign informed consent form before study entry. After publication of results for the primary endpoints, anonymised summary metadata and statistical code will be made openly available. The data will not include any information that could make it possible to identify a given participant.

**Trial registration number:**

Clinicaltrial.gov: NCT04026230, Eudra-CT: 2016-004774-17, protocol code: ESTO2, protocol date 10 September 2020 and version 6.

Strengths and limitations of this studyFirst randomised placebo-controlled phase 3 clinical study on effects of atorvastatin on prostate cancer progression during androgen deprivation therapy treatment.Multicentre study in Finland, Denmark, Estonia and Norway.As a limiting factor, only minority of prostate cancer cases are advanced and large proportion of potential participants are ineligible due to using statins already. Thus, study enrolment will take several years.

## Introduction

Prostate cancer (PCa) is the most common cancer in Finnish men and a major public health burden causing annually around 900 cancer deaths in Finland and the yearly costs caused by the disease are estimated to reach 180 million euros.^1 2^ However, not all prostatic malignancies are lethal; only 10%–20% of tumours advance to metastases and eventually into a fatal stage. Advanced PCa is treated by androgen deprivation therapy (ADT). Eventually, however, PCa progress despite the ADT treatment and forms state called castration resistance. Thus, castration resistance is clinically defined as a moment when PCa no longer responds to ADT treatment. Median time to castration resistance is 12–15 months and 45 months to death in patients who have started ADT for metastatic PCa.^3–7^ In men who start ADT for disease recurrence after primary treatment, median failure-free survival time is 33 months and 70 months to death.^3^

Blood cholesterol is likely a risk factor for PCa prognosis; risk of disease recurrence after primary treatment is significantly elevated in men with hypercholesterolaemia.^8^ Laboratory studies have demonstrated the importance of cholesterol for PCa cell growth.^9 10^ Furthermore, upregulation of intracellular lipid production and ensuing lipid accumulation is essential in surviving hypoxic tumour microenvironment.^11^ In PCa cells, it also assists in evading host-tumour immune response.^12^ Also, upregulation of intracellular cholesterol production appears to be central for development of castration resistance.^13^

Lipid metabolism is emerging as a new risk factor for PCa progression. The role of cholesterol is important in development of castration resistance, and inhibition of intracellular lipid production interferes with androgen receptor (AR) signalling essential for PCa progression.^13–15^ Cholesterol is precursor for intracellular androgen production, a central mechanism for PCa cells to overcome ADT.^13 15^ A recent study suggests that some of the serum basic lipid parameters may have increased association with development of castration resistance and metastasis especially in statin-naïve patients.^16^ Clarification of the role of lipid metabolism during ADT will likely provide new tools for control of disease progression and PCa treatment.

Use of cholesterol-lowering statin drugs is associated with lowered risk of PCa recurrence and progression; risk of PCa death is reduced by 30% compared with the non-users.^14 17 18^ The anticancer effect may be specifically against progression of the disease and the mechanisms driving it.^19^ Statins inhibit the cholesterol-synthesising mevalonate pathway, which is active in PCa cells.^10 20^ Besides cholesterol, this pathway also produces isoprenoid proteins which are critical for regulation of cell growth and other central cellular control processes.^20^ Furthermore, steroid hormones such as testosterone are metabolised from cholesterol, thus statins appear to target androgen metabolism, another crucial pathway for PCa growth.^21 22^

Statin use has been reported to prolong efficacy of ADT in PCa as it has been reported to prolong the efficacy of ADT for 8–10 months.^23 24^ Furthermore, statins have been linked to a prolonged response to androgen-signalling targeted drugs abiraterone and enzalutamide used in management of castration-resistant disease.^25 26^

Statins have not been found to affect PCa mortality in trials testing their efficacy in secondary prevention of cardiovascular disease.^27^ However, in these trials, cancer was often an exclusion criterion. On the other hand, it may be that statin treatment has more impact on hormone-dependent cancers which are underrepresented in these studies. In a randomised clinical trial focusing on PCa patients 80 mg of atorvastatin has been found to reduce tumour proliferation activity compared with placebo after minimum exposure of 21 days.^28^ Similar results were seen after treatment with fluvastatin, although in a non-randomised and uncontrolled setting.^29^ Nevertheless, clinical efficacy of statins in preventing progression of PCa has not been tested in a randomised placebo-controlled setting. Also, a recent post-hoc study of randomised clinical trial concluded that statin use was associated with decreased overall and PCa-specific mortality in men with ADT.^30^ Therefore, it is important to do a trial testing effects of statins specifically in PCa patients.

### Study objective

Primary objective for this phase III randomised double-blind placebo-controlled trial is to explore whether intervention with atorvastatin delays PCa progression that is, development of castration resistance compared to placebo during ADT for metastatic or recurrent PCa. Secondary objectives include exploring whether atorvastatin lowers PCa-specific or overall mortality compared with placebo, and to demonstrate whether changes in serum lipid parameters predict disease recurrence and occurrence of adverse tumour genomic traits predicting castration resistance among PCa patients during ADT.

## Methods and analysis

### Study setting

Study flow, study settings and other information are presented in figure 1 and table 1. The study recruitment target is 400 participants who start ADT as primary management of de novo metastatic PCa or as secondary management for PCa recurrence after localise treatment. Participants can be high-risk M0 or M1 stage, main inclusion criterion is that long-term ADT treatment is started. These men will be randomised 1:1 (200+200) to receive either 80 mg of atorvastatin daily or placebo until disease recurrence that is, development of castration resistance, death or maximum of ten years. Sample size is based on a power calculation from a previous retrospective study.^23^

**Figure 1 F1:**
[figure not shown]
Study flow with inclusion and exclusion criteria. ADT, androgen deprivation therapy.

**Table 1 T1:** Study setting of Impact of atorvastatin on prostate cancer after initiation of androgen deprivation therapy clinical trial

Study settings	
Primary registry and trial identifying no	Clinicaltrials.gov NCT04026230
Date of registration in primary registry	19 July 2019
Secondary identifying numbers	Eudra-CT: 2016-004774-17, Protocol code: ESTO2
Source(s) of monetary or material support	Tampere University Hospital, Finland
Primary sponsor	Tampere University Hospital, Finland
Secondary sponsor(s)	Helsinki University Hospital, Turku University Hospital, Central Finland Central Hospital, Kuopio University Hospital, Oulu University Hospital, Finland, Herlev Hospital, Denmark, University Hospital Tarto, Estonia, Vestfold Hospital Trust, Tønsberg, Norway
Contact for public queries	Tampere University Hospital, [name], PhD
Contact for scientific queries	Tampere University Hospital, [name], PhD
Public title	Impact of atorvastatin on prostate cancer progression after initiation of androgen deprivation therapy
Scientific title	Impact of atorvastatin on prostate cancer progression after initiation of androgen deprivation therapy— lipid metabolism as a novel biomarker to predict prostate cancer progression—phase 3, double-blind randomised clinical trial FinnProstata XV
Countries of recruitment	Finland, Denmark, Estonia, Norway
Health condition studied	Metastatic or recurrent prostate cancer
Intervention	Active comparator: Capsules of atorvastatin 80 mg, Placebo comparator: Similar capsules as in the atorvastatin arm, but without the active ingredient
Key inclusion and exclusion criteria	Inclusion criteria: Histopathologically confirmed metastatic adenocarcinoma of the prostate for which androgen deprivation or antiandrogen therapy is initiated no longer than 3 months before as the primary treatment Willingness to participate and signing of informed consent exclusion criteria: Statin use at the time of recruitment or within 6 months of it, Previous adverse effects during statin therapy, familial hypercholesterolaemia or very high total cholesterol, clinically significant renal or liver insufficiency, use of drugs that may interact with statins
Sexes eligible for study:	Male
Accepts healthy volunteers	No
Study type	Interventional, allocation: randomised, Intervention model: parallel assignment with 1:1 allocation ratio, Masking: double blind (subject, caregiver, investigator, outcomes assessor), Primary purpose: prevention, phase III
Date of first enrolment	July 2019
Target sample size	400
Recruitment status	Recruiting
Primary outcome(s)	Castration resistance
Key secondary outcomes	Lipid levels, Prostate cancer mortality and overall survival, Circulating cell free DNA, Fasting blood glucose, Occurrence of cardiovascular events during ADT, Quality of life

ADT, androgen deprivation therapy.

The study will be carried out in collaboration between urological departments of University Hospitals and central hospitals in Finland, the Herlev University Hospital in Denmark, the Tartu University Hospital in Estonia and Vestfold Hospital Trust in Norway (table 1).

Study data are collected and managed using REDCap electronic data capture tools hosted at Tampere University.^31 32^ Only the primary investigators, study nurses and registered study coinvestigator from each participating site will have access to the platform. All laboratory results, symptoms and results from imaging studies done at the discretion of the attending clinicians are recorded in the database. All clinical decisions besides the study drug, for example, use of early chemotherapy, abiraterone or other drugs in adjunct with ADT will be up to the discretion of the attending clinician and allowed but will also be recorded in the REDCap database.

Follow-up is continued until development of castration resistance, death or maximum of 10 years. Participants are given the opportunity to carry on with the intervention even after development of castration resistance to observe effects on survival. Unblinding will be performed after recruitment target has been reached and all participants have been followed for minimum of 12 months.

Castration resistance is defined as either PSA progression (three consecutive rises of PSA measured at least 1 week apart with two >50% increases over the nadir and PSA >2 ng/mL) or radiological progression (appearance of two or more lesions in bone scan or soft tissue enlargement as per RECIST criteria) while serum testosterone is at the castrate level (<50 ng/mL or 1.7 nmol/L).

For men who initiate statin use during the study period for clinical indications, the study drug is dropped but the study follow-up is continued. These men will be included in the final analysis according to the intention-to-treat principle within their allocated study arm.

In case of intolerable side effects as judged by either the participant or the attending physician, the study drug is stopped, and these men will be analysed according to the intention-to-treat principle.

Participants who discontinue follow-up or deviate from the study protocol for any reason will be given the chance to remain or return to follow-up to allow intention-to-treat analyses.

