### Study flow

Study flow and schedule is presented in figure 1 and table 2. Patients are recruited at urology outpatient clinic at urologists’ visits. If the inclusion criteria are met and the exclusion criteria are not and the participant signs informed consent form, he is given a study number (ranging between E-001 to E-400) and he receives either 80 mg atorvastatin or placebo according to the study arm randomly allocated for the study number. No blocking or other restrictions will be implemented for randomisation. Only the national study coordinator in each country will be able to see which study arm the participant has been randomised to. The participant will then receive first dose of the respective study drug randomised to his study number. The drug boxes and capsules containing atorvastatin and placebo will be identical in appearance. All researchers, nurses and study participants will remain blinded to the allocation sequence until termination of the study and closure of the study data.

**Table 2 T2:** Study flow and timing of the laboratory and blood sample collection

	Enrolment	Allocation	Follow-up‡			
Timepoint		0	6 months	12 months	18 months	24 months
Enrolment:						
Eligibility screen	x					
Informed consent	x					
Allocation		x				
Interventions:*						
Atorvastatin			x	x	x	x
Placebo			x	x	x	x
Assesments:						
Serum PSA (ng/mL)	x		x	x	x	x
Alkaline phosphatase (U/L)	x		x	x	x	x
Creatinine (µmol/L)	x		x	x	x	x
Serum creatine kinase (U/L)	x		x	x	x	x
Alanine aminotranspherase (U/L)	x		x	x	x	x
Fasting blood glucose (mmol/L)	x		x	x	x	x
Lipid levels (total cholesterol, LDL, HDL and triglycerides) (mmol/L)	x		x	x	x	x
Cell free DNA (subgroup)†	x					
QoL	x			x		x

*Allocation 1:1 to have eighter 80 mg atorvastatin or placebo daily

†Cell free DNA is measured before allocation and after occurrence of castration resistance.

‡Follow-up until disease recurrance, death or max. 10 years

HDL, high-density lipoprotein; LDL, low-density lipoprotein; PSA, prostate-specific antigen; QoL, quality of life.

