### Sample size calculation

In a cohort study by Harshman *et al*,^23^ among men starting ADT, 58% of the statin users and 75% of non-users of statins progress to castration resistance during median 5.8 years. We used these crude percentages for sample size calculations.

With alpha and beta values of 0.05 and 0.20 (power=0.80), sample size of 400 men will be enough to detect a risk difference with HR 0.65 (figure 2). We assume 10% drop-out rate in each study arm. The programme ‘PS—Power and sample size, V.3.1.2’ was used for the calculation.

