**Figure 2 F2:**
[figure not shown]
Sample size estimation with power 0.8 as a function of HR. Calculation was made based on study by Harshman *et al.*^23^

The median time to disease progression is assumed to be 12–15 months for patients with de novo metastatic disease and 33 months for patients recurring after primary therapy.^3–7^ Therefore, the intervention will continue until castration resistance, death, or for maximum of 10 years. Post hoc follow-up will continue after the intervention. A 3 months’ difference in time to castration resistance between the study arms will be considered clinically significant.

It has to be noted that the number of studies published on this topic is low and, in the absence of randomised evidence on this topic, the power calculation is based on results of epidemiological study prone to residual bias. Therefore, an interim analysis will be performed after the first 100 participants have met the primary endpoint, that is, progressed into castration resistance. Without lifting the blinding, the power calculations are repeated to verify whether the chosen sample size has adequate statistical power to detect statistically significant difference of the effect size observed between the randomisation groups at that time. If the calculations suggest that a larger sample size is needed for the trial, the study protocol will be amended with updated recruitment target.

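### The code is opened on a calendar rule with no event condition, while men may still be on study drug and at risk; this conflicts with the promised blinding and leaves the 80% power unsecured

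*Protocol article*

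**What the plan says.** **Unblinding.** Under Study setting, and again under Study flow, the article states: "Unblinding will be performed after recruitment target has been reached and all participants have been followed for minimum of 12 months". Neither place mentions events, says who is unblinded, or says whether the primary analysis is run on that date.

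**Blinding.** Study flow also says that researchers, nurses and participants "will remain blinded to the allocation sequence until termination of the study and closure of the study data". The abstract says that researchers, study nurses and patients are blinded for the whole trial. The one stated exception under Study flow is the national study coordinator, who can see the allocation.

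**Duration.** Study setting and Sample size calculation continue the intervention until castration resistance, death or 10 years. Study setting and Study flow let men stay on their assigned capsules after castration resistance; Study setting gives observation of survival as the purpose.

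**Power.** Sample size calculation takes from a retrospective cohort that "58% of the statin users and 75% of non-users of statins progress to castration resistance during median 5.8 years", adds "We used these crude percentages for sample size calculations", and concludes that a "sample size of 400 men will be enough to detect a risk difference with HR 0.65", at alpha 0.05 and power 0.80. It also states: "We assume 10% drop-out rate in each study arm". It gives no required number of events and no accrual period.

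**Interim look.** After 100 primary events the power calculation is repeated, and the recruitment target may be raised.

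**The concern.** Two things are at stake.

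The first is bias. If the code is opened 12 months after the last man enters, men who have not progressed continue on a treatment that they and their clinicians may now know. Imaging and added cancer treatment are at the clinician's discretion, and men who start a statin for clinical reasons stay in follow-up in their allocated arm. Knowledge of the allocation could therefore affect when progression is found, what else is given, and how men answer the quality-of-life questionnaire. Survival, a secondary endpoint, takes longest to mature and would be observed largely after the code is open. Blinding cannot be restored afterwards.

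The second is information. The power of a log-rank test depends on the number of events. The trial is sized from progression proportions reached over a median of 5.8 years, but the only stated condition for opening the code is a date. How many events exist on that date depends on accrual time and case mix, and the article fixes neither.

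**Working it through.** **Inputs from the article:** alpha 0.05, power 0.80, HR 0.65, N = 400 (1:1), 10% drop-out, 75% versus 58% progressed over a median of 5.8 years, median time to progression 12–15 months (de novo metastatic) and 33 months (recurrent), minimum follow-up 12 months.

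**Assumptions, not in the article:** two-sided test; exponential times; uniform accrual over 24 to 60 months (the article says only that enrolment takes several years); case mix; drop-outs contribute no events, so 360 men are evaluable.

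**1. Events required.** Schoenfeld: D = 4(1.960 + 0.842)² / (ln 0.65)² = 169.2, so 170 (power 80.2%; 169 gives 79.96%). Freedman's formula gives 175.

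**2. The plan's 400.** At full 5.8-year maturity:
- Two proportions, 75% versus 58%: 120 per arm, 240 in total, and 240/0.9 = 267 with drop-out.
- By events: 170 / 0.665 = 256, and 256/0.9 = 285 with drop-out.

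Full maturity therefore does not return 400. A survival calculation with staggered entry can. The control median implied by the cohort is 5.8 × ln 2 / ln 4 = 2.9 years = 34.8 months. With 60 months' accrual and 12 months' minimum follow-up the event fraction is 0.473, so 170/0.473 ≈ 360, and 360/0.9 = 400. The stated size is thus compatible with the 12-month rule, but only at an accrual length that the article does not state.

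**3. Events and power at the trigger.** For hazard λ, accrual A and minimum follow-up F = 12 months, the event fraction is 1 − [exp(−λF) − exp(−λ(A+F))] / (λA), averaged over the arms with hazards λ and 0.65λ. Power = Φ(|ln 0.65|·√D/2 − 1.96).

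Example, 34.8-month median, A = 36: control fraction 0.438, atorvastatin 0.316, mean 0.377. Then 0.377 × 360 = 136 events, and Φ(0.4308 × √136/2 − 1.96) = 71%.

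| Control median | Events at A = 24 / 36 / 48 / 60 months (360 men) | Power |
|---|---|---|
| 34.8 months (cohort-implied) | 115 / 136 / 154 / 170 | 64 / 71 / 76 / 80% |
| 33 months (all recurrent) | 120 / 141 / 160 / 176 | 65 / 73 / 78 / 82% |
| Half 13.5, half 33 months | 170 / 193 / 212 / 227 | 80 / 85 / 88 / 90% |
| 12–15 months (all metastatic) | 208 to 289 | 87 to 96% |

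If all 400 men contribute, the first row becomes 68 / 75 / 80 / 84%. For comparison, at 5.8 years with HR 0.65 the event fraction is (0.75 + 0.594)/2 = 0.672. That is 242 events among 360 men and 92% power.

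**4. Men still at risk at the trigger,** as 400 minus expected events among 400, ignoring deaths and losses: 211–272 at the cohort-implied rate, 204–267 if all are recurrent, 148–211 for the even mix, and 79–169 if all are metastatic.

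**5. The blinding statements side by side.** The two rules agree only if the study ends and the data close 12 months after the last enrolment. The 10-year treatment and follow-up rule, and continued treatment to observe survival, say that they do not.

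**The case against.** The strongest reply is that the shortfall depends on the scenario. The 34.8-month median is slower than either median the plan assumes, and it treats a crude proportion over a median follow-up as survival at a fixed time. Two years' accrual, the source of the 64%, fits poorly with enrolment lasting several years: first enrolment was in July 2019 and the trial was still recruiting in an article published in April 2022. Men who stop the drug stay in intention-to-treat follow-up, so counting only 360 is conservative. An even case mix reaches 80% at every accrual length tried. All of this stands.

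The 100-event look is also a real, though partial, safeguard: a larger recruitment target would postpone the trigger. It sets no final event count, however. An event target may stand in the full protocol or analysis plan, and 12 months is a minimum. That tempers the power point but does not reconcile the opposing blinding statements.

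Three stronger readings are tempting, and the article does not support them:
- A reader might infer that the trial is underpowered. The table shows that this depends on unstated accrual and case mix.
- A reader might infer that 400 is a miscalculation, because full maturity needs fewer than 300. Step 2 shows that 400 follows under one plausible accrual period, and the sample-size figure is not available to check.
- A reader might infer an error because a 3-month "difference in time to castration resistance between the study arms will be considered clinically significant", while HR 0.65 corresponds to 6.5–8.1 months at medians of 12–15 and 17.8 months at 33. A relevance threshold and a design effect are different quantities, and the plan claims no power for 3 months.

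**Conclusion.** The point holds in a limited form. The contradiction over blinding rests on the text alone: the stated trigger can open the code while treatment and follow-up continue, against two promises that the blind is kept. Its reach, about 150 to 270 of 400 men still free of castration resistance (79 to 169 if all are metastatic), rests on exponential times, accrual of 24 to 60 months, and no deaths or losses.

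The power point is that 80% is not secured by a calendar rule. Across the cohort-implied and even-mix scenarios, power at the trigger runs from 64% to 90%. This does not show that power will be missed. Because the article does not say who is unblinded, opening the code to everyone is what the wording permits, not something the plan is known to intend.

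**What to change.** 1. Reconcile the abstract, Study setting and Study flow so that one rule states when the code is opened and to whom.
2. Run the primary analysis at the later of 170 castration-resistance events or 12 months' minimum follow-up for every man.
3. At that point unblind only the analysis team. Keep site staff, researchers involved in follow-up, and participants blinded until data closure. The national coordinators already have access to the allocation under Study flow, so state their role separately.
4. State the power in events, with the accrual and follow-up assumptions that lead to 400.

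The change is one of wording and needs no extra patients. The cost is possibly a later primary analysis. At the cohort-implied rate with 360 men, 170 events need a minimum follow-up of about 28, 22.5, 17.5 or 12 months for accrual of 24, 36, 48 or 60 months, a delay of up to about 16 months (28 − 12). For an even case mix the expected delay is nil.

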### Inclusion and exclusion criteria

Inclusion criteria for participants are histopathologically confirmed metastatic adenocarcinoma of the prostate or high-risk M0 stage recurrent PCa for which androgen deprivation or antiandrogen therapy is initiated no longer than 3 months before recruitment, willingness to participate and signing of informed consent (figure 1).

Exclusion criteria for participants are regular statin use at the time of recruitment or within 6 months of it, previous adverse effects during statin therapy, familial hypercholesterolaemia or very high total cholesterol (9.3 mmol/L or above), clinically significant renal (serum creatinine above 170 µmol/L) or liver insufficiency (serum alanine aminotransferase more than two times above the upper limit of normal range), and use of drugs that may interact with statins (St John’s Wort, HIV protease inhibitors, ciclosporin, macrolide antibiotics, fucidic acid, phenytoin, carbamazepine, dronedarone or oral antifungal medication) (figure 1).

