### Study endpoints

Primary endpoint is the time to disease progression after starting ADT/antiandrogen therapy. Secondary endpoints are (1) PCa-specific mortality and overall survival, (2) change in serum cholesterol during the intervention and its role in predicting time to disease recurrence in the placebo arm, (3) occurrence of adverse tumour traits predicting development of castration resistance in circulating cell free DNA, (4) changes in fasting blood glucose during ADT, (5) occurrence of cardiovascular events during ADT and (6) Quality of life (QoL) during ADT.

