Subgroup analyses will be performed stratified by type of ADT or antiandrogen therapy initially selected; GnRH agonists/antagonists, antiandrogen, orchiectomy or other. Men who start with antiandrogen therapy often change to GnRH agonists/antagonists or orchiectomy when PSA increases during ADT. This is allowed and PSA recurrence during antiandrogen therapy is not considered as disease progression as serum testosterone needs to be at castrate level as well for meeting the primary endpoint.

Another subgroup analysis will be stratified by whether or not the participants have received local therapy (radiation or surgery) for PCa in addition to ADT and by type of additional therapy participant has received; docetaxel, abiraterone, enzalutamide or apalutamide at hormone-sensitive stage in addition to ADT.

All analyses will include only participants with available data, imputations will not be used. Detailed statistical analysis plan is published before final data analysis. All analyses are performed using SPSS V.27, Stata V.17 and R V.4 statistical softwares.

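### The castrate-testosterone limit in the primary endpoint is given as two figures about 100-fold apart, which probably reflects a unit misprint, and they must be reconciled

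*Protocol article*

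**What the plan says.** The definition stands in the Study setting section of the protocol article, after Table 1. It begins "Castration resistance is defined as either PSA progression (three consecutive rises of PSA measured at least 1 week apart" and goes on to set size conditions on the PSA rise, with radiological progression as the alternative route. Both routes count only "while serum testosterone is at the castrate level (<50 ng/mL or 1.7 nmol/L". This is the only place in the article that puts a number on the castrate level.

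The number matters for three other statements:

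- Study endpoints: "Primary endpoint is the time to disease progression after starting ADT/antiandrogen therapy". The Statistical methods section makes clear that this is time to castration resistance.
- Inclusion and exclusion criteria: men are eligible with disease "for which androgen deprivation or antiandrogen therapy is initiated no longer than 3 months before recruitment", so some may enter on antiandrogen therapy.
- Statistical methods, paragraph on subgroups by type of ADT: a PSA recurrence on antiandrogen therapy is not treated as progression, and the reason given is that "serum testosterone needs to be at castrate level as well for meeting the primary endpoint".

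**The concern.** The definition joins a mass concentration and a molar concentration with the word or, as though they were the same limit in two units. They are not, and no other part of the article settles which is meant.

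The limit is a decision rule in the primary endpoint. It separates progression that counts from progression that does not, and the article relies on it to keep PSA rises on antiandrogen therapy out of the event count. Castration resistance also sets the timing of the interim analysis (after 100 such events) and is one of the stated ends of follow-up. A reader or programmer cannot apply both figures: for any testosterone value lying between them, one says castrate and the other says not.

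**Working it through.** **Inputs**

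- Limit in mass units: 50 ng/mL (Study setting).
- Limit in molar units: 1.7 nmol/L (Study setting).
- Molar mass of testosterone, M: not in the article. Assumed to be 288.42 g/mol from the formula C19H28O2, with 288 to 289 shown as a range.

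**Formula**

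nmol/L = (ng/mL × 1000) / M

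**Step 1. The pair as printed**

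50 × 1000 / 288.42 = 173.4 nmol/L (173.0 for M = 289; 173.6 for M = 288).

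The stated 1.7 nmol/L is not reproduced. The ratio is 173.4 / 1.7 = 102 (101.8 to 102.1 over the range of M).

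**Step 2. Could rounding or the assumed molar mass explain it?**

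For 50 ng/mL to equal 1.7 nmol/L, M would have to be 50 × 1000 / 1.7 = about 29,400 g/mol. The assumption about M is therefore not what drives the result, and rounding cannot close the gap.

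**Step 3. The alternative reading of the mass unit**

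50 ng/dL = 0.5 ng/mL, and 0.5 × 1000 / 288.42 = 1.73 nmol/L (1.730 to 1.736), which rounds to 1.7.

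In the other direction, 1.7 × 288.42 / 1000 = 0.490 ng/mL = 49.0 ng/dL.

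So the pair is consistent if the mass unit is per dL. The 102-fold gap is a factor of 100 from mL against dL, and the remainder is the rounding of 1.73 to 1.7.

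**Step 4. What the two limits do to the endpoint**

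| Serum testosterone | By 1.7 nmol/L | By 50 ng/mL |
|---|---|---|
| below 1.7 nmol/L | castrate | castrate |
| 1.7 to about 173 nmol/L | not castrate | castrate |
| about 173 nmol/L or above | not castrate | not castrate |

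The two limits disagree only in the middle row. A man in that row becomes an event under the ng/mL figure only if he also meets the PSA or radiological criterion.

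**The case against.** The best defence is that the intended limit can be recovered. The molar figure stands in the same parentheses, the pair becomes coherent with one letter changed (mL to dL), and the Statistical methods section shows that the condition is meant to keep some men out. That section also states the antiandrogen exclusion in words, so a site following the text has that sentence as well as the number. If testosterone is recorded in nmol/L, the mass figure is never used. The article condenses a protocol (version 6) that is not shown, and the misprint may exist only in the article.

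Most of this stands, and it limits the consequences. It does not remove the contradiction, because the worded exclusion takes its reason from the castrate level, and the only number for that level is the inconsistent pair.

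A reader might infer more than the documents support:

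- **That every PSA failure on antiandrogen therapy would become a primary event.** The testosterone condition creates no event by itself; the PSA or radiological criterion must be met too. The exclusion is also stated in words, and the article says that men on antiandrogens often change treatment when PSA rises, so some may do so before meeting the full PSA rule.
- **That the ng/mL limit would exclude nobody.** That needs a range of testosterone values in this population, which the article does not give.
- **That the error would differ by country.** The article does not say which unit any site uses for testosterone.
- **That events already recorded are wrong.** Nothing shows that the ng/mL figure was ever applied.
- **That one arm would be favoured.** Allocation is randomised and double-blind, so a misapplied limit would be expected to act in both arms by the same rule. The more likely cost is a diluted, less interpretable endpoint.

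**Conclusion.** The point holds as a contradiction in the primary-endpoint definition. The figures in "<50 ng/mL or 1.7 nmol/L" differ about 102-fold and cannot both be the limit. The only outside input is the molar mass, and no plausible value of it changes the conclusion. The pattern suggests a misprint of the mass unit.

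The effect on the trial depends on which figure is in use, and the article does not show this. If the ng/mL figure were applied, men between 1.7 and about 173 nmol/L who also met the PSA or radiological criterion would be counted as castration resistant, against the reasoning in the Statistical methods section. The number of such men is unknown, since the article gives neither testosterone values nor the share starting on antiandrogens. No effect on the hazard ratio or the power can be calculated from it. The text needs correcting because it is a decision rule for the primary outcome, not because any misclassification has been shown.

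**What to change.** 1. Reconcile the two figures to one threshold in consistent units in the endpoint definition. If a second unit is shown, it should be a true conversion of the first.
2. Check which unit and limit the full protocol and the REDCap database carry.
3. Recheck recorded castration-resistance events against the reconciled limit only if the ng/mL figure is found to have been used there.

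The first step is a one-line correction and the second a short look-up. The third costs a review of recorded events, and only if the second shows that it is needed. The sample size calculation does not use this limit and is unaffected by the correction.
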